### Outcome assessments

#### Effectiveness

All outcome measures for the two groups (usual care group and the intervention group) are collected at baseline and follow-up. The primary outcome is change in health-related quality of life (SF-36 and KCCQ) from baseline to follow-up. SF-36 total score is used as the primary outcome, and the subscales are used as secondary outcomes. The secondary outcomes for effectiveness are changes in the mortality rate and physiological measurements such as blood pressure, pulse, and weight from baseline to follow-up. Mortality rate is considered only if enough participants are included to satisfy the power calculation for this secondary outcome. The clinical impact of telehealthcare is considered to be positive if no increase in mortality is observed and if pulse and blood pressure are lowered.

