#### Cost assessment

The main outcome for cost is the incremental cost-effectiveness ratio (ICER). The ICER is measured as the total cost per quality-adjusted life-year (QALY) gained from baseline to follow-up. It is anticipated that telehealthcare will increase the participants’ quality of life, but no difference in mortality is expected. Additionally, it is expected that telehealthcare will reduce cost, particularly due to a reduction in the number of admissions/readmissions and outpatient visits [20].

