### Sample size

A sample size calculation for effectiveness was performed using OpenEpi (http://www.openepi.com/Menu/OE_Menu.htm). Conservative estimates were applied for the minimal clinically important difference (change equal to 5 for the SF-36 physical component summary). With a power of 80%, groups of equal size, a standard deviation of 15, and a two-sided *p* value of <0.05, the required sample size is estimated to be at least 284 participants. With an expected loss to follow-up of 10%, the total required sample size is estimated to be at least 316 participants.

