#### Effectiveness

To evaluate effectiveness, differences between the intervention group and the control group with regard to SF-36 scores, mortality rates, and physical measurements from baseline to follow-up will be analyzed. The outcome will primarily be analyzed using two-sample paired statistics (e.g., two-sample paired *t* test), such that the differences from baseline to follow-up will be assessed between groups.

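### Mortality is considered only if recruitment satisfies a power calculation, yet the trial's own rule for a positive clinical impact needs the mortality result

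*Protocol article*

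**What the plan says.** Under Outcome assessments, Effectiveness, the protocol article gives mortality secondary status: "The secondary outcomes for effectiveness are changes in the mortality rate and physiological measurements such as blood pressure, pulse, and weight from baseline to follow-up". It then restricts that outcome: "Mortality rate is considered only if enough participants are included to satisfy the power calculation for this secondary outcome". The sentence after that sets the rule for the clinical conclusion: "The clinical impact of telehealthcare is considered to be positive if no increase in mortality is observed and if pulse and blood pressure are lowered".

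Elsewhere the restriction is absent. The abstract lists change in mortality as a secondary outcome without qualification. Statistical methods, Effectiveness, says that differences between the arms "with regard to SF-36 scores, mortality rates, and physical measurements from baseline to follow-up will be analyzed".

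Two further statements bear on the point. Outcome assessments, Cost assessment, says that "no difference in mortality is expected". The Sample size section holds the only calculation in the article, and it concerns quality of life ("change equal to 5 for the SF-36 physical component summary"), not deaths.

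**The concern.** Whether a declared outcome is evaluated should not depend on how many patients happen to be recruited. Here it does, against a threshold that the article does not state, and the outcome is also needed for the trial's own verdict. If the threshold is missed, the mortality part of the clinical-impact rule either cannot be assessed or is met only because nobody looked.

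The article says that the results will inform decisions on a national standard for heart failure care. Deaths also matter for reading the primary results: follow-up quality of life can be collected only from survivors, and quality-adjusted life-years depend on survival.

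**Working it through.** **The passages side by side**

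| Place in the protocol article | Mortality |
|---|---|
| Abstract, Methods/design | secondary outcome, no condition |
| Outcome assessments, Effectiveness (condition) | considered only if recruitment satisfies its power calculation |
| Outcome assessments, Effectiveness (next sentence) | no observed increase is required for a positive clinical impact |
| Statistical methods, Effectiveness | will be analysed, no condition |

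The second and third rows cannot both be followed if the condition fails. The first and fourth rows promise what the second may withhold.

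**The plan's own calculation**

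Inputs from Sample size: difference 5, SD 15, power 80%, two-sided 0.05, equal groups, 10% loss. With (1.960 + 0.842)² = 7.849:

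- n per arm = 2 × 7.849 × 15² / 5² = 141.3, so 142, and 284 in total.
- With loss: 284 / 0.90 = 315.6, so 316.

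Both stated figures reproduce. Neither says anything about deaths.

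**What a mortality calculation would require**

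The article gives no death rate, effect or margin. Assumed here: 12-month control mortality p1 of 5%, 10% or 15%; risk ratio 0.7, so p2 = 0.7 × p1; two-sided 0.05; 80% power; deaths counted in all randomised patients. Sample sizes compared: 600 (expected, from the abstract; 300 per arm) and 316 (158 per arm).

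Formulas:

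- n per arm = 7.849 × [p1(1 − p1) + p2(1 − p2)] / (p1 − p2)²
- power = Φ(|p1 − p2| / SE − 1.96), with SE = √{[p1(1 − p1) + p2(1 − p2)] / n}

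Worked case, p1 = 0.10 and p2 = 0.07:

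- n per arm = 7.849 × (0.0900 + 0.0651) / 0.03² = 1,352.6, so 1,353, and 2,706 in total.
- With 300 per arm, SE = √(0.1551 / 300) = 0.0227 and 0.03 / 0.0227 = 1.32, so power = Φ(1.32 − 1.96) = 26%.

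| Assumed control mortality | Total N for 80% power | Power with 600 | Power with 316 |
|---|---|---|---|
| 5% | 5,672 | 15% | 10% |
| 10% | 2,706 | 26% | 16% |
| 15% | 1,718 | 38% | 22% |

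**Scenarios in which 600 is enough**

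The first two use the two-proportion formula with pooled variance under the null, which gives slightly larger numbers.

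- Halving of risk at 15% mortality (15% v 7.5%): 556 in total.
- A 1.5-fold increase at 20% mortality (20% v 30%): 588 in total.
- Non-inferiority with true rates of 5% in both arms and a 5-point margin: n per arm = 7.849 × 2 × 0.05 × 0.95 / 0.05² = 298.3, so 299, and 598 in total.

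So whether 600 patients satisfy the condition depends on which rate, effect or margin is chosen.

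**What can be reported without adequate power**

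With 300 per arm and 10% mortality in both, the 95% interval for the risk difference has half-width 1.96 × √(2 × 0.10 × 0.90 / 300) = 0.048, or about 4.8 percentage points. That is imprecise, but it still tells the reader which increases the data can exclude.

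**The case against.** The strongest reply is that this is a journal article. It refers to a power calculation for mortality as if one exists, and such a calculation is commonly left to the full protocol. That stands: its absence from the article is not a fault, and a reader should not infer that none was made.

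It also stands that expecting no difference does not leave a calculation without a target. It could be built on a minimum important difference or on a margin for harm, just as the quality-of-life calculation uses a minimal important difference rather than an expected effect.

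Other stronger readings are tempting and are not supported:

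- A reader might call mortality the main safety outcome. The article lists it as a secondary effectiveness outcome, although the clinical-impact rule does use it as a check for harm.
- A reader might conclude that mortality will normally be dropped. That rests on assumed rates and an unseen threshold, and 600 patients suffice in some scenarios.
- A reader might infer that deaths will not be recorded or compared at all. The article commits to intention-to-treat analysis and CONSORT reporting, and being considered may mean formal evaluation only.
- A reader might infer that utilities after death will be imputed. The article mentions multiple imputation only if necessary and says nothing about deaths.

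Finally, the list in the statistical methods is general, and the specific condition could be read as qualifying it. This weakens that contradiction. It does not touch the one between the two adjacent sentences under Outcome assessments, which lies in the stated text and not in an omission.

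**Conclusion.** The point holds as an internal conflict with a practical consequence: a declared secondary outcome depends on achieved recruitment, while the trial's own rule for a positive clinical impact cannot be applied without it. This conclusion needs no assumption about death rates.

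The likelihood that the condition fails does need assumptions. On 5% to 15% control mortality and a risk ratio of 0.7, power falls well short of 80% at both 316 and 600 patients. With a larger effect, a higher death rate or a wide margin, 600 can be enough.

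The primary outcome, the stated sample size and the cost-effectiveness ratio do not hinge on this sentence. It should be fixed, but it does not undermine the design.

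**What to change.** Delete the conditional sentence under Outcome assessments, Effectiveness. In its place, state that all-cause mortality will be reported by arm in all randomised patients whatever the sample size, as an effect estimate (for example a risk difference or hazard ratio) with a 95% confidence interval, and that this comparison is not powered and carries no claim of significance. Align Statistical methods, Effectiveness, with that wording, so that the clinical-impact rule always has a mortality result to refer to.

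The cost is an edit to the text and a little extra analysis of an outcome that is already declared. The downside is a wide interval, which the label makes plain. The design, the sample size and the primary analysis stay as they are.

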Studies of telehealthcare show positive results regarding health outcomes and quality of life in other patients with chronic illness [9]. Some studies of feasibility indicate that the use of telehealthcare may also lower the costs of healthcare [10–13]. Additionally, several studies have shown promising results for telehealthcare with regard to HF [14, 15], whereas others have not found an effect [16, 17]. These studies have led to increased political and clinical attention to telehealthcare as a means of improving outcomes for patients with HF and lowering costs. However, there is a need for large-scale clinical trials with cost-effectiveness assessments in telehealthcare research [14].

In Denmark, healthcare decision makers have agreed to support the advancement of research into the health effectiveness and cost-effectiveness of telehealthcare for patients with HF. As part of the national Danish plan for the dissemination of telemedicine, a full-scale randomized trial has been planned for the North Denmark Region (Region Nordjylland). The North Denmark Region is one of five regions in Denmark and has healthcare responsibility for approximately 580,000 people. The project is based on experiences with and solutions arising from the TeleCare North COPD trial [18]. The results of the trial will inform political and clinical decisions regarding how to implement a telehealthcare solution as a national standard for HF healthcare in Denmark.

The aims of this trial are separated into two focus areas. The first area aims to evaluate whether a specific telehealth solution that is serving as a supplement to usual healthcare increases quality of life for patients with HF compared with the quality of life of those receiving usual healthcare alone. The second area aims to evaluate the cost-effectiveness of this specific telehealth solution.

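### The only written rule for a positive clinical impact leaves out quality of life, the primary outcome, and the plan does not reconcile the two

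*Protocol article*

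**What the plan says.** The Background section of the protocol article sets the effectiveness aim as whether telehealth, added to usual care, "increases quality of life for patients with HF compared with the quality of life of those receiving usual healthcare alone". Under Outcome assessments, Effectiveness, the plan states: "The primary outcome is change in health-related quality of life (SF-36 and KCCQ) from baseline to follow-up". It then narrows this to one score: "SF-36 total score is used as the primary outcome, and the subscales are used as secondary outcomes".

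The same paragraph ranks the other measures below this: "The secondary outcomes for effectiveness are changes in the mortality rate and physiological measurements such as blood pressure, pulse, and weight from baseline to follow-up". One of them is conditional: "Mortality rate is considered only if enough participants are included to satisfy the power calculation for this secondary outcome". The paragraph closes with the verdict rule: "The clinical impact of telehealthcare is considered to be positive if no increase in mortality is observed and if pulse and blood pressure are lowered".

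The Sample size section plans for a 5-point difference on the SF-36 physical component summary, with SD 15, 80% power and a two-sided 5% level. This gives 284 participants, or 316 after allowing for 10% loss to follow-up. Under Outcome assessments, Cost assessment, the expectation is: "It is anticipated that telehealthcare will increase the participants’ quality of life, but no difference in mortality is expected".

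**The concern.** The closing rule is the only sentence in the article that says when the clinical impact of the intervention counts as positive, and it does not mention the outcome the trial was designed around. Nothing in the Effectiveness paragraphs, under either Outcome assessments or Statistical methods, says how this verdict relates to the quality-of-life result.

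This is not a detail that an article leaves to a fuller document. The article states a rule, and the rule as stated permits a prespecified positive label after a null or adverse primary result. It also permits that label to be withheld after a successful one. What the trial may claim is therefore left open.

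**Working it through.** **Side by side.**

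| Element | Quality of life | Mortality | Pulse, blood pressure |
|---|---|---|---|
| Effectiveness aim (Background) | yes | no | no |
| Rank (Outcome assessments) | primary | secondary, conditional | secondary |
| Basis of sample size | yes (SF-36 physical component) | no | no |
| Rule for positive clinical impact | **no** | yes | yes |

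The defect can be read from this table. The arithmetic below only illustrates its consequences.

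**The plan's own figures.** n per arm = 2 × 15² × (1.960 + 0.8416)² / 5² = 141.3, so 142 per arm and 284 in total. 284 / 0.9 = 315.6, so 316. Both figures reproduce. Power is 80.2% at 142 per arm, and 98.3% at 300 per arm (the 600 expected participants, without loss).

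**How the rule was read.** Deaths in the telehealth arm are no more than in control, and the between-arm point estimates for pulse, systolic and diastolic pressure are all lower. The sentence names no comparator or test, so this reading is itself an assumption.

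**Assumptions not in the documents.** Mortality 5–15% and equal in both arms. Correlation 0.6 between systolic and diastolic pressure, 0.1 between pulse and pressure, and 0 with quality of life. Effects on pulse and pressure from 0 to 5 standard errors (SE).

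**Mortality clause.** With equal true mortality and equal arms, P(no observed increase) = ½ + ½ × P(tie). At 142 per arm and 10% mortality, the SD of the difference in deaths is √(2 × 142 × 0.1 × 0.9) = 5.06. P(tie) is then about 0.399 / 5.06 = 0.079, and the clause passes with probability 0.54. Over 5–15% mortality and both sample sizes it passes in 52–55% of trials.

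**Pulse and pressure clause with no true effect.** P(all three lower) = 1/8 + [arcsin 0.6 + 2 × arcsin 0.1] / (4π) = 0.125 + 0.067 = 0.192.

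**Whole rule with no true effect.** 0.192 × 0.54 = 0.10. Other correlations give 7–13%. If blood pressure means systolic alone, independent of pulse, the result is 0.25 × 0.55 = 0.14.

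**How often the verdicts differ** (simulation, 1,000,000 trials per scenario; primary success is a two-sided 5% test in favour of telehealth):

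| True SF-36 gain | Pulse/pressure effect | Mortality clause | N | Primary succeeds | Rule met | Verdicts differ |
|---|---|---|---|---|---|---|
| 5 | none | applied | 284 | 80% | about 10% | 74% |
| 5 | none | applied | 600 | 98% | about 10% | 88–89% |
| 5 | 1 SE | applied | 284 | 80% | 34–36% | 59–60% |
| 5 | 2.8 SE or more | applied | 284 | 80% | 53–55% | 47–48% |
| 5 | 2.8 SE or more | not applied | 284 | 80% | over 99% | 20% |
| 5 | 2.8 SE or more | not applied | 600 | 98% | over 99% | 2% |
| 0 | none | applied | 284 | 2.5% | about 10% | 12–13% |
| 0 | 2.8 SE or more | applied | 284 | 2.5% | 53–55% | 53–55% |
| 0 | 2.8 SE or more | not applied | 284 | 2.5% | over 99% | about 97% |

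Check of the first row: 0.802 × (1 − 0.104) + 0.198 × 0.104 = 0.74.

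**Adverse case.** The rule contains no quality-of-life term, so under independence a true 5-point loss leaves its pass rate unchanged. With a clear fall in pulse and pressure at 284, about 0.802 × 0.54 = 43% of trials would combine a significant loss on the primary outcome with a positive clinical impact.

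**The case against.** The strongest reply is that the sentence concerns clinical impact, comes directly after the secondary outcomes and uses only those. It can be read as an interpretation of the mortality and physiological measures beside a quality-of-life primary that already has its own aim, rank and sample size. Any trial with a quality-of-life primary and physiological secondaries can give different answers on each, and that alone is no fault.

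Much of this stands, and it rules out several stronger readings.

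- A reader might infer that success is defined in two incompatible ways. The article never calls the rule the criterion for trial success and never says it replaces the primary outcome. The two are unreconciled, not logically incompatible.
- A reader might infer from the first rows of the table that the verdicts would conflict in most trials. The documents give no SD, effect or correlation for pulse or blood pressure and no mortality rate, so no frequency follows from them. The figures also mix the omission of quality of life with the direction-only reading and with whether the mortality clause is applied.
- A reader might infer that decision makers would act on this rule. The Discussion ties adoption as a national standard to cost-effectiveness.
- The absence of weight from the rule adds nothing: the article states no favourable direction for it.

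What the reply does not answer is the wording. If the sentence is only a summary of secondary measures, the article does not say so. It makes an unqualified statement about the intervention, under the Effectiveness heading, that a report could cite as prespecified.

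**Conclusion.** The point holds in this form: the only written rule for a positive clinical impact rests on secondary outcomes alone, omits the primary outcome, and has no stated relation to it. That conclusion is textual and needs no assumption. Its frequency is illustrative only: the spread of about 2% to 97% comes from the assumed effects, mortality rates and correlations and from whether mortality is considered, and no single value in it is an estimate for this trial. The sample size figures are correct and unaffected. The wording should be corrected, because it governs what the trial may conclude; the planned data and comparisons are not at fault.

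**What to change.** Under Outcome assessments, Effectiveness, tie the conclusion to the primary outcome, for example:

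> The conclusion on effectiveness rests on the between-group difference in the primary quality-of-life score. Mortality and the physiological measures are reported with confidence intervals as a descriptive summary of secondary outcomes; they cannot by themselves support or override that conclusion.

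Then delete the clinical-impact sentence, or keep it explicitly labelled as that descriptive summary. The change should be dated and made before outcome data by arm are examined.

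The cost is one or two sentences, with no new data, patients or procedures, and no clinical rule is set or altered. The downside is that the trial gives up a second route to a favourable headline.

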### Measurement assessment

The data, which include measurements (blood pressure, pulse, and weight) and symptom-specific information from the tablet questionnaire will be assessed by a specially trained nurse. The responsibility is shared between the municipalities and the outpatient healthcare centers, depending on where the patients are affiliated.

Data assessment implies that the patient’s data are seen, interpreted, and evaluated to determine whether there should be an intervention. The data assessments will be conducted at fixed intervals (typically one or two times per week). After each assessment, an acknowledgement will be sent to the patient. If a patient’s measurements are not received as expected, the patient will be contacted. The measurements are classified as being within the normal range or outside the normal range. These predefined thresholds are adjusted if necessary during the first 14 days of measurements to fit the individual patient. The predefined thresholds are systolic blood pressure 170–100 mmHg, diastolic blood pressure 90–50 mmHg, pulse 80–55 beats/minute, and weight ±2 kg.

If the clinician observes abnormal measurements, several options are available:The clinician can contact the patient and ask for a new measurement if the measurement is considered to be less suitable.The clinician can contact the patient to assess the patients condition.It is possible to start a self-treatment plan for the patient.If the clinician judges that the patient is cable of taking contact to his or her own general practitioner, the patient is asked to do so.The clinician can contact the patient’s general practitioner directly.

The intervention needed is always a clinical judgment based on the patient’s measurement and possibly a subsequently contact with the patient. It should be noted that the goal is to help the patient understand his or her own data and thereby empower the patient to take responsibility for handling the disease.

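### The clinical-impact verdict is not tied to a between-arm test, an interval or a named pressure measure, and its mortality condition may be dropped

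*Protocol article*

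**What the plan says.** Under Outcome assessments, Effectiveness, the protocol article lists mortality, blood pressure, pulse and weight as secondary outcomes. It then sets a verdict: the clinical impact of telehealthcare is "considered to be positive if no increase in mortality is observed and if pulse and blood pressure are lowered".

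The sentence just before that one makes mortality conditional: "Mortality rate is considered only if enough participants are included to satisfy the power calculation for this secondary outcome". The article gives no such calculation. Its Sample size section covers only the SF-36 physical component summary.

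Under Statistical methods, Effectiveness, a comparison of the two arms is planned for SF-36, deaths and the physical measurements, with a t test on changes as the example, "such that the differences from baseline to follow-up will be assessed between groups". The verdict does not refer to this analysis, and the analysis does not refer to the verdict.

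Under Cost assessment the article adds that "no difference in mortality is expected".

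**The concern.** The article states a success criterion but does not fix how it is judged. Three things are open or weak.

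- **Lowered** is not tied to the planned between-arm test, to an interval or to a minimum size. Blood pressure could mean systolic, diastolic or both.
- **Mortality** is judged on what is observed. A point estimate at or below zero would count as no increase, whatever its uncertainty.
- **Mortality may be left out** under the preceding sentence. The verdict then either cannot be reached or loses its only safety condition, and the article does not say which.

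At stake is a statement of positive clinical impact that could arise by chance, or with no real evidence on deaths, in a nonblinded trial where the reading could be settled after the results are known. The article says that the results are to inform decisions on national implementation.

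**Working it through.** **Inputs from the article.** Sample size: difference 5, SD 15, 80% power, two-sided 0.05, 284 evaluable, 316 with 10% loss. The abstract expects 600 participants.

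**Inputs assumed, because the article gives none.** Mortality over follow-up of 1–15%. Correlation between the pulse difference and one pressure difference of 0–0.3. Systolic–diastolic correlation of 0–0.6 where both are required. Mortality independent of the other measures.

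**The plan's own figure.** n per arm = 2 × 15² × (1.96 + 0.84)² / 5² = 141.3, so 142 per arm and 284 in all; 284 / 0.90 = 315.6, so 316. This reproduces. With 600 enrolled and 10% lost, 600 × 0.90 / 2 = 270 per arm.

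**Step 1. No observed excess of deaths when true risks are equal.** With X and Y independent binomials, P(X ≤ Y):

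| Mortality | 142 per arm | 270 per arm |
|---|---|---|
| 1% | 0.626 | 0.588 |
| 5% | 0.555 | 0.540 |
| 10% | 0.540 | 0.529 |
| 15% | 0.533 | 0.524 |

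The values exceed one half because ties count as no increase.

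**Step 2. Physiology by direction alone, no effect.**

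- Pulse and one pressure measure: 1/4 + asin(r)/(2π). This is 0.250 at r = 0, 0.282 at r = 0.2 and 0.298 at r = 0.3.
- Pulse, systolic and diastolic: 1/8 + (sum of the three asin r)/(4π). This is 0.125 if all are independent, 0.176 with systolic–diastolic r = 0.6, and 0.208 with r = 0.2 to pulse as well.

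So without mortality the rule is met in about 12–30% of trials.

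**Step 3. Full rule, no effect (step 1 × step 2).** Lowest corner: 0.125 × 0.524 = 0.066. Highest corner: 0.2985 × 0.626 = 0.187. At 5% mortality and 142 per arm, pulse plus one pressure measure gives 0.250 × 0.555 = 0.139 at r = 0 and 0.282 × 0.555 = 0.156 at r = 0.2. The range is roughly 7–19%.

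**Step 4. Lowered read as significantly lower between arms.** The chance that two standard normal differences both fall below −1.96 is 0.06% at r = 0, 0.16% at r = 0.2 and 0.24% at r = 0.3. This is before any mortality condition.

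**Step 5. The mortality condition when deaths truly rise.** Assume 13% with telehealth and 10% with usual care.

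| | 142 per arm | 270 per arm |
|---|---|---|
| P(no observed excess) | 0.24 | 0.15 |
| P(no significant excess, pooled z < 1.96) | 0.88 | 0.81 |

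Reading the mortality condition as no significant increase therefore makes it weaker. An interval shows why: at 10% in both arms the 95% half-width is 1.96 × √(2 × 0.10 × 0.90 / 142) = 7.0 percentage points, or 5.1 at 270 per arm.

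**The case against.** **A direction-only rule is one reading, not what the article says.** The word observed attaches to mortality only, and a between-group analysis is planned for the physical measurements. On that reading a chance positive is very unlikely (step 4). This stands, so the 7–19% and 12–30% figures describe one reading under stated assumptions. They are also not ceilings, since higher correlations raise them.

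**The power condition guards against an underpowered mortality claim.** Detecting 10% against 13% with 80% power needs about {1.96√(2 × 0.115 × 0.885) + 0.84√(0.13 × 0.87 + 0.10 × 0.90)}² / 0.03² ≈ 1,770 per arm. If the unshown calculation targets a difference of that size, mortality would not be considered and the step 5 rates would not arise. That is fair, but it leaves the verdict with no safety condition and no statement of what then happens.

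**Test details for secondary outcomes often sit in the analysis plan.** True. Here, however, the article itself states the criterion, and states it loosely.

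A reader might infer more than the article supports:

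- *That the rule has no comparator, so regression to the mean could satisfy it.* The Effectiveness paragraph opens with both groups, and the analysis compares changes between groups. Regression to the mean threatens only a single-arm reading, because randomized arms share it.
- *That scoring lower values as good contradicts the ranges under Measurement assessment* ("systolic blood pressure 170–100 mmHg, diastolic blood pressure 90–50 mmHg, pulse 80–55 beats/minute"). Those are thresholds for reviewing one patient's readings, adjusted to the individual. A lower group mean does not conflict with them.
- *That the trial's type I error is inflated.* The outcomes are labelled secondary and the primary test is unaffected. The Discussion ties possible national adoption to cost-effectiveness, not to this verdict.

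**Conclusion.** The point holds as a badly fixed criterion for secondary outcomes. Two parts need no assumption: the verdict is not connected to the planned between-arm analysis, an interval or a named pressure measure; and it depends on mortality, which the preceding sentence may remove.

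The size depends on the reading. With no effect, direction alone meets the rule in roughly 7–19% of trials, or 12–30% without mortality. Requiring significance between arms cuts the physiological part to about 0.06–0.24%. These figures rest on mortality of 1–15% and the correlations listed above, none of which the article gives. On any reading, an observed absence of excess deaths says little about safety at this trial's size.

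**What to change.** Replace the verdict sentence. Report systolic pressure, diastolic pressure and pulse as secondary outcomes, each as a baseline-adjusted between-arm difference with a 95% confidence interval. Report the mortality difference with its 95% confidence interval in every case, without making it depend on a power calculation. State that absence of harm will not be concluded from a point estimate or from mortality having been left out.

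If the investigators prefer to keep a verdict, the least that is needed is to tie it to the planned between-group analysis, name the pressure measure, judge mortality by its interval, and say that no verdict is given if mortality is not analysed.

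The change is wording only and needs no extra data. The cost of the main option is one secondary headline claim.
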